##### Physical activity program optimization/adaptations to the program structure

The Seniors Exercise Park program is a structured 12-week exercise program with incremental increase in the number and/or type of exercises and exercise duration throughout the 12 weeks [24]. The exercise program has been delivered to over 80 older people without cognitive impairment who are living in the community. Any modifications to the delivery of the overall exercise program and/or individual exercise sessions (e.g. exercise length, session duration) due to safety concerns, and other reasons (e.g. mental or physical fatigue) will be documented. During the maintenance phase (exercise after completion of the formal research supervised component, from 12 to 24 weeks post baseline), the exercise behaviors of each participant (activity and duration) will be monitored and recorded by the exercise instructor and by a supervisor from the facility (e.g. facility staff will encourage and supervise ongoing participation and use of the exercise park equipment). Field notes (post-session reflection notes) will be completed by the research staff noting down any variations of the program, participant’s behavior and any other relevant aspects identified by the staff.

##### Supervision needs

Our previous and current research suggests that one supervisor for 6–10 participants who are functionally independent (no walking aid, or with limited usage of walking aid) is safe. We anticipate that some people will have mobility limitations as well as cognitive impairment, and therefore will aim initially for one qualified instructor (exercise physiologist/physiotherapist) and another supervisor (from the aged-care staff) for up to 3–4 participants. As we expect participants to improve throughout the exercise program, the supervision ratio will be reassessed every two weeks and be adjusted accordingly. The number of participants at each session and number of supervisors will be recorded and monitored throughout the program, and will be used in analysis and reporting.

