## Abstract

**Background:**

While the underlying neuropathology of dementia is not curable, interventions and treatment, such as physical activity, can offer physical and functional gains leading to better mobility, independence and quality of life. The Seniors Exercise Park program is an evidence-based physical and social activity program using an innovative design in outdoor exercise equipment specifically designed for older people. This unique program has never been tested with older people living with dementia. This study will evaluate the feasibility of delivering the Seniors Exercise Park program for people living with mild to moderate dementia in residential aged-care. This study will identify the optimal physical activity program, evaluate the safety of equipment usage and determine optimal supervision needs. The potential physical, social, quality of life and cognitive benefits of participation in the Seniors Exercise Park program will also be examined.

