### Assessments

#### Primary outcome

The primary outcomes for this study are the feasibility, safety and supervisory needs associated with the program:

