#### The Seniors Exercise Park program

##### 12-week structured supervised exercise program

Participants will undergo a 12-week supervised exercise intervention program twice a week using the Seniors Exercise Park. Participants will perform exercises that focus on strength, balance, coordination, mobility and flexibility as detailed in our previous work [15, 24]. Examples of the exercises can be found here https://youtu.be/PaYuCMtnlYk. The exercise park sessions will be provided two times a week (each class approximately 1 to 1.5 h duration) and will be supervised by a qualified accredited exercise physiologist or physiotherapist with the assistance of another supervisor (aged-care staff; physiotherapist/diversional therapist). Each session will consist of 5–7 min warm-up exercises, followed by 45–75 min on the equipment stations, and will conclude with 5–7 min of cool down exercises. The exercise classes will include 3–4 participants and will be circuit-based. To maximise social interaction and enjoyment, morning/afternoon tea will be organised following the exercise sessions.

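### Supervision needs are a primary outcome, but the measure named for them, per-session head-counts, cannot by itself separate need from rostering and attendance

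*Protocol article*

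**What the plan says.** The Primary outcome section states: "The primary outcomes for this study are the feasibility, safety and supervisory needs associated with the program". The abstract's Background says that the study will "evaluate the safety of equipment usage and determine optimal supervision needs".

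The Supervision needs section describes the starting point: the team "will aim initially for one qualified instructor (exercise physiologist/physiotherapist) and another supervisor (from the aged-care staff) for up to 3–4 participants". Because participants are expected to improve, "the supervision ratio will be reassessed every two weeks and be adjusted accordingly". It then names the data: "The number of participants at each session and number of supervisors will be recorded and monitored throughout the program", and says that these numbers will go into the analysis and reporting.

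The section on the 12-week structured supervised exercise program describes the same sessions without any adjustment. An exercise physiologist or physiotherapist leads "with the assistance of another supervisor", and "The exercise classes will include 3–4 participants and will be circuit-based". The Randomisation section is consistent with that class size, since each block supplies 3–4 intervention participants.

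**The concern.** A primary outcome needs a measure that responds to the thing it is named after. Here the article does not leave the measure open: it names participant and supervisor counts. The study sets the supervisor count, and allocation and attendance set the participant count. Neither is an observation of how much help a resident needed.

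The fortnightly adjustment could bring need into the counts, because staff would be acting on what they saw. The article names no record of why a change was made, however, and the section describing the structured classes mentions no change at all.

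If the counts are reported as the supervision result, the trial may largely hand back its own staffing plan, blurred by absences. A facility could read a statement about optimal supervision as evidence for safety and staffing decisions, which head-counts alone would not support.

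**Working it through.** **Inputs**
- Target of 12 participants per group, 3–4 exercise groups, about 15% dropout and 20 completers of 24 (Sample size estimation and justification).
- Class size 3–4 (Randomisation; Supervision needs; 12-week structured supervised exercise program).
- Two supervisors at the start, reassessed every two weeks (Supervision needs).
- Two sessions a week for 12 weeks (12-week structured supervised exercise program).
- Attendance target of at least 70% in the structured phase and at least 60% over six months (Feasibility; Statistical analysis).

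**The plan's own figures.** 24 × (1 − 0.15) = 20.4, against 20 stated. 12 / 4 = 3 and 12 / 3 = 4, so 3–4 groups of 3–4 exercisers fit together. The planning figures are coherent and are not at issue.

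**Ratio by design.** Ratios are written as one supervisor to (participants present / supervisors present).
- Two supervisors, all present: 3 / 2 = 1.5 and 4 / 2 = 2, so 1:1.5 to 1:2.
- One supervisor, all present: 3 / 1 = 3 and 4 / 1 = 4, so 1:3 to 1:4.

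**Effect of absence alone.** Assume independent absences, each resident attending with probability a, and two supervisors throughout. Mean present = class size × a, and P(full class) = a^(class size).

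| Class | a | Mean present | Ratio | P(full) |
|---|---|---|---|---|
| 4 | 0.60 | 2.4 | 1:1.2 | 0.130 |
| 4 | 0.70 | 2.8 | 1:1.4 | 0.240 |
| 4 | 0.85 | 3.4 | 1:1.7 | 0.522 |
| 3 | 0.60 | 1.8 | 1:0.9 | 0.216 |
| 3 | 0.70 | 2.1 | 1:1.05 | 0.343 |
| 3 | 0.85 | 2.55 | 1:1.275 | 0.614 |

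At the trial's own attendance target, supervision therefore looks more intensive than planned (1:1.4 against 1:2 for a class of four) with nobody's need having changed.

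**Same ratio, different causes.** A class of four with one absent gives 3 / 2 = 1.5, the same as a full class of three. A full class of four with two supervisors gives 4 / 2 = 2. The same class with two absent and one supervisor gives 2 / 1 = 2.

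**Where need could enter.** Reassessment every two weeks over 12 weeks gives at most 12 / 2 = 6 decisions per class, or 3 × 6 = 18 to 4 × 6 = 24 over 3–4 classes. These decisions carry the staff's judgement of need. The data named for the outcome show that the supervisor count changed, not whether improvement, an incident or staff availability was the cause.

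**The two descriptions side by side.** Supervision needs presents two supervisors as the starting arrangement, to be adjusted. The section on the structured programme presents an instructor plus another supervisor, in classes of 3–4, with no mention of change. A reader cannot tell from these which elements may vary: the second supervisor, the class size or both.

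**The case against.** The strongest reply has four parts.

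*Staffing is not frozen.* Supervision needs calls the arrangement initial and provides for adjustment, and the section on individual and group exercise progression expects programme modifications and says that variations will be recorded. The structured-programme section can be read as the starting format. This stands: it would be wrong to infer that two supervisors are fixed for 12 weeks. What remains is that the two descriptions should be made to agree and that an adjustment is informative only if its reason is known.

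*Much more than head-counts is recorded.* Incidents are recorded at each session (Safety), as are programme modifications and field notes, motivation for each participant, engagement (GOME) and wandering, and delivery staff complete a survey after each exercise group (Overall feedback). One motivation level even describes a resident who has to be persuaded to take part. This also stands, and in a pilot of this size reading the counts alongside such material is reasonable. But the article does not link these records to the supervision ratio, and none systematically codes the prompting, stand-by or hands-on help given to each resident. They supply context, not the measure.

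*Participants and supervisors are counted separately, and attendance is itself an outcome.* An absence can therefore be told apart from a staffing change. That is correct, and it limits the absence argument to the ratio. It does not supply the reason for a staffing change.

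*This is an article.* Adjustment criteria and session forms may sit in the full protocol, and a supervision summary may sit in an analysis plan. Their absence here is therefore not counted as a fault. The point rests on the measure that the article does name.

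**Conclusion.** The point holds in a limited form. For a primary outcome described as determining optimal supervision needs, the named data are per-session counts that mainly reflect planned staffing and attendance. By themselves they cannot separate need from rostering or absence. The size is as tabulated: 1:1.5 to 1:2 by design, and a mean of 1:1.4 for a class of four at 70% attendance, with that class full in 24% of sessions. The attendance figures assume independent absences and two supervisors throughout. Shared causes of absence, such as illness in the facility, would change the spread but not the means.

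Three stronger readings are tempting and are not supported:
- *That the trial cannot determine supervision needs at all.* Staff judgement can enter through the fortnightly adjustment, and the other session records give descriptive evidence.
- *That no ratio beyond 1:4 could ever be seen, so the 1:6–10 cited from work with functionally independent people is out of reach.* The 1:4 figure follows from classes of 3–4 in the structured phase. The maintenance-phase section states neither a class size nor a two-supervisor format for weeks 12–24.
- *That the trial fails to show how need differs between mild and moderate dementia.* The article does not list that comparison as an aim; severity is a randomisation stratum.

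This should be corrected, but it does not threaten the trial's other feasibility and safety outcomes. No view is taken on which staffing ratio is right.

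**What to change.** 1. Reconcile Supervision needs with the section on the 12-week structured programme, saying which of class size and number of supervisors may change during the 12 weeks. This asks for consistency and does not call for any particular ratio.
2. Add to the existing per-session record one code per resident for the highest assistance given: none, verbal prompting, stand-by or hands-on.
3. On the same record, note planned and actual staffing and the reason for any change.
4. Report assistance level descriptively by programme week as the supervision-needs outcome, with the counts as context. With about 12 exercisers, any split by severity should be labelled exploratory.
5. Restate the aim in the abstract, and wherever it recurs, as the assistance needed under the supervision levels actually used. The qualification matters because help given can also depend on how many staff are present.

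The cost is a small recording burden for the instructor: at full attendance, 12 exercisers × 24 sessions (2 × 12 weeks) = 288 single codes in the structured phase, plus a line per session on staffing. No extra staff, participants or visits are needed.

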#### Secondary outcomes

A comprehensive suite of physical function (strength, balance, functional mobility), psychosocial (quality of life, depression, loneliness), cognitive, and falls risk and falls history will be assessed. Physical activity participation, engagement, social interaction, mood and enjoyment data will also be collected.

#### Physical function measures

Physiological measures of strength, balance and functional mobility will be assessed using the following validated tests:(i)Functional lower limb muscle strength using the five times sit to stand test [25]. Participants will be asked to sit on a chair (43 cm high) and stand up (with arms crossed over their chest) five times. The time taken to complete the sit to stand will be measured (seconds).(ii)Exercise tolerance and functional mobility using the two-minute walk test [26]. Participants will walk in a marked area for 2 min at their comfortable pace. The distance covered during the 2 min will be recorded. The length of walkway will be around 10–15 m, based on available length of the facility corridor.(iii)Dynamic balance using the step test [27]. Participants will be asked to place one foot onto a 7.5cm-high step and then back down to the floor repeatedly as fast as possible for 15 s. The number of steps completed in the 15s period for each leg will be recorded. The step test is a test of dynamic standing balance, only takes approximately 1 min to administer, has been shown to have good retest reliability (ICC = .868) in people living with dementia [28], and demonstrated significant improvement in another Seniors Exercise park study (ENJOY translation study) in older people without cognitive impairment [19].(iv)Walking speed using the 4 meters walk test [29]. Participants will be asked to walk 4 m at their usual walking pace. Gait speed will be defined by distance (in meters) divided by time (in seconds). Participants will start walking 2 m before the 4m walkway, and finish walking 2 m after the 4m walkway.

#### Psychosocial, cognitive and quality of life health outcomes

A set of valid, reliable and widely used instruments (specifically for older people and those living with dementia) for cognitive screening, quality of life, socialisation, daily activity engagement and depression will be used.(i)*The Montreal Cognitive Assessment (MoCA)* is a brief 30-question cognitive screening test. It assesses several cognitive domains: attention and concentration, executive function, memory, language, visuoconstructional skills, conceptual thinking, calculations and orientation [30].(ii)*Health-related quality of life* will be assessed using two instruments: the Quality of Life in Alzheimer's disease scale (QoL-AD) and the EQ-5D-5L. The QoL-AD will be administered via interview with the person and is comprised of 13 items (physical health, energy, mood, living situation, memory, family, marriage, friends, self as a whole, ability to do chores, ability to do things for fun, money and life as a whole) [31]. The EQ-5D-5L is a generic instrument to assess health related quality of life that comprises five dimensions (mobility, self-care, usual activities, pain/discomfort and anxiety/depression) as well as overall utility score. The EQ-5D-5L allows comparison across multiple populations [32], and is the most widely published and used health utility scale for which there are multiple utility conversions available for populations internationally.(iii)*Fear of falls* will be assessed using the Iconographical Falls Efficacy Scale [33]. The IFES is a valid and reliable 10 items scale that assesses fear of falling in older people with cognitive decline.(iv)*Loneliness* will be assessed using the UCLA 3-Item Loneliness Scale. The UCLA Loneliness Scale includes three dimensions of loneliness: relational connectedness, social connectedness and self-perceived isolation [34, 35].(v)*Depression* will be assessed using the short version Geriatric Depression Scale (GDS-15) [36]. The GDS-15 is a 15-item instrument where a score of 0 to 5 is considered normal and a score greater than 5 suggests depressive symptoms.(vi)*Social isolation and social support* will be assessed using the short version 6 items Lubben Social Network Scale (LSNS-6) [37]. The score ranges between 0 and 30 where higher scores indicate more social engagement(vii)*Engagement with daily activity* will be assessed by aged-care staff using the Pool Activity Level (PAL). The PAL is a widely used, validated, measure of engagement with activity for older people living with dementia [38]. The researchers/aged-care staff will rate residents’ ability to plan and perform during nine common daily activities—bathing/washing, dressing, eating, contact with others, group work skills, communication skills, practical activities, use of objects, reading/looking at a newspaper/magazine. Each activity is scored on a 4-point scale: 1 = ‘planned—needing little or no help with everyday activities’; 2 = ‘exploratory—able to carry out familiar activities in familiar surroundings’; 3 = ‘sensory—limited ability to perform an activity’; 4 = ‘reflex’—unable to perform basic everyday tasks without assistance’. The caregiver ticks the one that most accurately describes the individual’s performance of that activity over the preceding two weeks.

#### Falls risk assessment

(i)*The Falls Risk Assessment Tool (FRAT)* will be used to assess fall risk [39]. The FRAT is a 4-item falls-risk screening tool for sub-acute and residential care: with risk factors scored to reflect graded risk of low, moderate and severe risk.

#### Perceptions and feedback of the physical activity program –from aged-care staff and from participants

##### During the physical activity program delivery

Mood and enjoyment will be recorded *from the participants* and will include the following:

*Mood—*This will be assessed at the beginning of each session and will include a 5-point Likert scale using a visual smiley face card as follows: 0—sad, depressed, down; 2—in the middle (not happy, not sad) and 4—happy (high, awesome, great).

*Enjoyment*—At the end of the exercise session participants will be asked if they enjoyed the program, and to rate their level of enjoyment on a 5-point Likert scale using a visual smiley face card as follows: 0—not at all, 2—in the middle (neutral), 4—enjoyed it very much (had fun).

During the physical activity program motivation to participate, engagement and wandering behavior will be recorded *by the staff* (research instructor, facility staff) as follows:

*Motivation to participate*—participants’ motivation will be assessed by the exercise supervisor at each exercise session based on their observation and interpretation of participants’ expression, verbal prompt and body language [40]. A 5-point Likert scale will be used as follows: 0—no motivation (present without participating), 1—low motivation (needs to be convinced to participate), 2—moderate motivation (attends the activity without being positive or negative), 3—high motivation (participates with positivity), and 4-very high motivation (participates very positively) [40].

##### Group observational measurement of engagement (GOME)

The GOME will be used to evaluate engagement in the physical and social activity and includes engagement on an individual and group levels [41]. On an individual level using a Likert scale, the engagement assessment includes one variable pertaining to participation in the group (attendance duration), three variables that assess engagement levels (engagement—amount of time participants are attentive to the group activity; active participation, and attitude toward the activity) and one variable that assesses sleep or sleep-like symptoms during the group activities for each participating individual.

On a group level, engagement will include record of number of participants in the group, positive (smiling, positive comments to others) and negative (angry comments toward group members) interactions using a 6-point Likert scale.

##### Wandering behavior

In circumstances where participants suddenly stop exercising without any particular reason (e.g., unrelated to fatigue, muscle soreness) and start wandering (walking off) around the park area, a staff member will ensure their safety and assist them to return to the park or to be seated in the resting area. Participants who walk off will be intermittently encouraged to re-join the exercise group. The staff will also document the behavior (description, duration and time occurred).

##### General motivation and engagement behavior at selected time points throughout the program

Motivation to go to the activity will be assessed at 5 time points: at the beginning of the structured physical activity program (week 1), halfway through (week 6) and at the end (week 12), halfway through the maintenance phase (week 18), and at the completion of the maintenance phase (week 24).

Motivation will be assessed using a 5-point Likert scale [0, very negative (never wants to or usually does not want to go to sessions, despite motivating attempts); 1, negative (needs to be motivated to go to sessions, which they usually do); 2, neither positive nor negative (goes to sessions without being motivated); 3, positive; 4, very positive] [40].

##### Overall feedback

At the completion of the 12-week exercise intervention, participants will be asked about their overall experience and to provide feedback about the exercise program. Feedback from the aged-care staff (staff who are involved in the project delivery) will also be collected at the completion of each exercise group using a survey (a questionnaire incorporating open ended and rating scale questions).

### Exercise Park intervention

#### The Seniors Exercise Park equipment

The exercise park equipment is outdoor playground equipment specifically designed for older people to improve strength, balance, joint movements, and mobility and function (Fig. 2). It comprises multiple equipment stations that target specific function or movement (upper and lower limb) such as shoulder range of movement, static and dynamic balance, and functional movement such as walking up/down stairs and sit to stand. The ground surfaces are non-slippery rubber (softfall) suitable for any playground equipment (Fig. 2). The area is also covered by waterproof sail shade cover.

